## Abstract

**Background:**

Older Chinese adults in the UK are more likely to be physically inactive and face unique cultural and socioeconomic barriers to physical activity (PA) compared with the general population, yet they lack tailored interventions. Using findings from an evidence review and qualitative interviews, and guided by the Behaviour Change Wheel framework, we developed a culturally appropriate PA promotion package to enhance the capability, opportunity, and motivation of older Chinese adults in the UK to engage in PA.

**Aim:**

This study aims to assess the feasibility and acceptability of conducting a randomised controlled trial (RCT) of culturally appropriate PA promotion strategies among older Chinese adults in the UK.

**Methods/design:**

This is a two-arm pragmatic feasibility RCT. Community-dwelling individuals who self-identify as Chinese, reside in the UK, are aged 60 years and older, and do not meet the World Health Organization (WHO) PA recommendations (i.e. < 150 min moderate PA or balance/strength exercise < 2 times per week) will be recruited. Participants will be randomised to receive either the culturally appropriate PA promotion strategy package or the WHO PA recommendation leaflet. Outcome data will be collected at baseline, 12 weeks, and 18 weeks post-randomisation. Primary outcomes will include feasibility measures (e.g. recruitment, compliance, adherence, and follow-up rates), intervention acceptability (qualitative interviews), and both subjective PA levels (PA Scale for the Elderly) and objective PA levels (Realalt 3DTriSport 3D Pedometer). Secondary outcomes will include the Brief COM-B (Capability, Opportunity, Motivation—Behaviour) questionnaire, physical function assessments (Short Physical Performance Battery, SPPB), and quality of life (Control, Autonomy, Self-realisation, and Pleasure-12,CASP-12). The feasibility of the study will be evaluated based on the pre-specified progression criteria.

**Discussion:**

This is the first study to assess the feasibility and acceptability of conducting an RCT of a culturally appropriate PA promotion strategy package among older Chinese adults in the UK. The findings from this study will inform improvements in PA promotion strategies and guide the development of a full-scale RCT, with the ultimate goal of creating culturally appropriate, sustainable interventions to improve the health and well-being of older Chinese adults in the UK.

**Trial registration:**

The study protocol was registered on the Open Science Framework on 19 November 2024 (https://doi.org/10.17605/OSF.IO/XQHJS).

**Supplementary Information:**

The online version contains supplementary material available at 10.1186/s40814-025-01693-7.

## Introduction

The Chinese population is one of the largest ethnic minority groups in the UK [1]. According to the most recent census data from 2021, the Chinese ethnic group in England and Wales comprised 445,646 people, accounting for 0.7% of the total population. While a majority of individuals from Chinese ethnic groups are of working age (16 to 64 years), there is still a notable percentage (6%) aged 60 and above [2], including those who migrated at a younger age and grew old in the UK, as well as those who migrated later in life to join their migrant families. In this paper, we use the term “older Chinese adults” to be consistent with academic writing practice. However, when interacting with our participants, we use the phrase “Chinese seniors” (“长者”) in line with community preferences as suggested by our public and community involvement and engagement (PCIE) advisors.

The well-being of older adults from ethnic minority groups has gained increased attention from researchers and policymakers [3]. Compared with the native population, older Chinese adults in the UK face more health problems and adopt less healthy lifestyles due to additional cultural, economic, and socioeconomic challenges [4]. For example, older Chinese adults in the UK are more likely to be physically inactive compared to their native counterparts, despite the well-documented benefits of physical activity (PA) [5, 6]. According to Ethnicity Facts and Figures, in the 55–74 age group, the Chinese ethnic group had a lower proportion classified as “physically active” compared to both the White British population and the national average [7]. On one hand, the low language proficiency and cultural barriers diminish their willingness, opportunity, and capability to participate in local PA programmes. On the other hand, compared to the native population, there are fewer resources and services specifically tailored to this ethnic minority group [5].

PA promotion interventions have been tested to increase the engagement of older adults in PA [8]. We conducted a systematic review of evidence on the use of PA promotion interventions for older adults from the Chinese diaspora and found that no intervention has been developed specifically for older Chinese adults in the UK. This highlights the importance of identifying culturally appropriate PA promotion strategies for this population. We also held a series of qualitative interviews with older Chinese adults in the UK, and found that factors influencing their PA behaviour are related to capability, opportunity, and motivation, as outlined in the COM-B (Capability, Opportunity, Motivation-Behaviour) framework [9], ([name], [name], [name], [name], [name]: Culturally appropriate physical activity promotion strategy package among older Chinese adults in the UK: a feasibility randomised control trial protocol, Unpublished).

Based on findings from a systematic review and interviews with the target population, supported by PCIE activities, we identified a series of Behaviour Change Techniques (BCTs) to enhance the capability, opportunity, and motivation of older Chinese adults to engage more effectively in PA. These strategies are presented as a three-part package, comprising culturally appropriate PA booklets, three monthly workshops, and a virtual social media support group.

Since this is the first PA promotion package specifically designed for older Chinese adults in the UK, this study seeks to conduct a feasibility randomised controlled trial (RCT) to evaluate key study procedures—such as recruitment, randomisation, attrition, data collection, data analysis, and outcome measure suitability. Additionally, this study will include qualitative interviews with participants to assess the acceptability of the culturally appropriate PA promotion strategy package.

This study will answer the following research questions:

Study preparation stageWhat is the willingness among older Chinese adults in the UK to participate in this study?What is the willingness among older Chinese adults in the UK to undergo randomisation?

For older Chinese adults who participate in the studyAre participants willing to remain in the study for its entire duration?Are they willing to engage in PA promotion strategies, including attending workshops, using the logbook, wearing the pedometer and joining the social media group?What are their perceptions of the PA promotion strategies?

Data collection and analysisAre they willing to participate in assessments and complete the data collection at the three time points?Are the outcome measures appropriate and acceptable for older Chinese adults in the UK?

Effectiveness questionsHow do older Chinese adults’ subjective and objective PA, physical function, and quality of life change after the intervention in both the intervention and control groups?

## Methods

### Study design

This is a two-arm pragmatic feasibility RCT study with an exploratory design framework. Alongside the trial, qualitative interviews will be conducted to evaluate the acceptability of the PA promotion strategy package, as well as the trial procedures, from the perspective of older Chinese adults in the UK. We report the protocol of the feasibility RCT following the CONSORT 2010 statement for randomised pilot and feasibility trials [10]. The study protocol has been registered in the Open Science Framework (10.17605/OSF.IO/XQHJS).

### Study setting and participants

#### Study setting

This feasibility study will be conducted in the community setting of Manchester, UK, which is known for having a substantial Chinese population. While the Chinese diaspora is geographically dispersed throughout the UK, Manchester stands out as one of the regions with the largest Chinese population, with approximately 3.0% (12,644) of all Chinese individuals residing there [11].

#### Eligibility criteria for participants

We will recruit participants who meet the following inclusion criteria:Adults aged 60 years or above;Self-identified as Chinese ethnicity;Speaking either Cantonese, Mandarin, and/or English;Able to read and write Chinese or English;No time requirement for their stay in the UK, but they should have settled in the UK as residents and not as tourists.Self-report not meeting the PA guidelines for older adults (engaging in less than 150 min of moderate-level PA each week and performing balance, strength, and flexibility exercises less than twice a week);Self-report being able to walk around at home independently;Can provide informed consent.

We however will exclude:Those who self-report that they already meet the PA guidelines (engaging in more than 150 min of moderate-level PA each week and performing balance, strength, and flexibility exercises more than twice a week), as this study focuses on older Chinese adults with insufficient PA.Those who plan to be away from Manchester for more than 2 months during the intervention period.Participants with diseases where exercise is contraindicated will be excluded to ensure the safety of the participants (see Table 1). A self-reported approach will be used to identify these conditions, including cognitive impairment, as it is considered more acceptable by PCIE participants than formal assessments such as the MMSE (Mini-Mental State Examination), which were viewed as burdensome. To mitigate potential bias, the research team will monitor participants throughout the study. Participants who show signs of impairment after giving consent, such as difficulty completing data collection or following instructions, will be excluded.

**Table 1 Tab1:** List of conditions contraindicating exercise participation

Participants who self-report any of the following diseases will be excluded:
o Uncontrolled pain;
o Uncontrolled angina;
o Major heart surgery in the last 6 months
o Resting SBP > 180 mmHg or resting DBP > 100 mmHg
o Tachycardia > 100 bpm
o Acute systemic illness (cancer, pneumonia)
o Visual or vestibular disturbances
o Significant drop in BP during exercise
o Unstable or acute heart failure
o Unable to maintain seated upright posture due to neurological deficits
o Recent injurious fall without a medical examination
o Serious impaired cognition (to the extent of being unable to follow simple movement instructions)
o Any other clinical condition that the person’s GP or clinician considers would make them unsuitable for participation in an exercise programme

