	**Motivation**				
** Booklet—page 6**	**Motivation**	Education Modelling	5.1. Information about health consequences 5.3. Information about social and environmental consequences 6.2. Social comparison 16.3 Vicarious consequences	A page provides examples/stories of how PA has benefited other Chinese seniors in the UK in terms of health, social connections, and emotional well-being	“*What’s the point? I used to be very active, but my husband died two years ago. I just don’t have interest in anything, including physical activity*” *“I’ve worked very hard my whole life, and now I’ve just become a bit lazy, you know? I just want to take it easy, like watching TV or playing mahjong with my friends.”*
** Booklet—page 7**	**Opportunity**	Enablement	3.1. Social support (unspecified)	A page offers guidance on how to find additional support, such as from family members, peer support and the health care system	“*I’m not really sure what type of exercise suits me, and the GP usually doesn’t discuss exercise with me. You know, the appointment time is very limited*.” *“I live by myself, and my grandson calls me to remind me to exercise every morning… so I just walk around inside my house.”*
** Booklet—page 8**	**Opportunity**	Enablement	3.1. Social support (unspecified) 7.1. Prompts/cues	A page provides information about existing local Chinese PA programmes	“*I just moved to the UK. I enjoyed exercising when I was in Hong Kong, but I don’t know about the exercise programs here. If I knew, I would love to join*.”
** Additional booklet-** Otago Exercise Booklet	**Capability**	Training	4.1. Instruction on how to perform the behaviour 9.1 Credible source	The Chinese version of Otago Home Strength and Balance Booklet	“*I only walk, and I walk at least half an hour a day. I don’t know how to do strength and balance exercises.”* *“Sometimes, I follow exercise videos on my phone, although I’m not sure if I’m doing them correctly*.”

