### Control group (WHO leaflet group)

In the control group, participants will receive the printed leaflet of recommendations from the WHO on PA for older adults [19]. Participants will be encouraged to follow these guidelines, 150–300 min of moderate or 75–150 min of vigorous aerobic activity per week, along with balance and strength exercises twice weekly, at a time and place convenient to them. No additional support will be provided. Participants in the control group will also be provided with pedometers to collect their steps at the three time points.

The study will span 18 weeks, comprising a 12-week intervention phase and a 6-week follow-up phase. During the intervention phase, participants in the intervention group will attend workshops and receive motivational and reminder messages via a social media group. In the follow-up phase, they will be encouraged to continue their PA behaviour independently without further workshops or messages. Participants in the control group will be encouraged to follow the WHO PA guidelines during the 18-week study period and, after the study concludes, will receive the culturally appropriate PA booklet and be invited to attend one workshop.

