The progression criteria in this study are shaped by the characteristics and context of the target population. Although ethnic minority groups, including older Chinese adults in the UK, are often described as hard to reach, the research team has built trust with this community through sustained engagement and previous research activities, which helps ensure successful recruitment. The study specifically targets older Chinese adults who do not currently meet recommended PA guidelines. While eligibility criteria were initially considered as part of the progression plan, findings from earlier research and feedback from the PCIE group confirmed that most older Chinese adults in the UK are physically inactive. This makes the eligibility criteria easily achievable and therefore less critical as a progression indicator for this feasibility study. In addition, compared with traditional clinical trials focusing on medical interventions, behaviour change interventions such as PA promotion are viewed by the PCIE group as more acceptable. This is likely to further support recruitment, retention, acceptability, and safety. Taken together, this context supports the use of relatively strict recruitment criteria, aiming to recruit 100% of the intended sample within the planned timeframe to ensure the feasibility of a future full RCT. More flexible thresholds for retention and adherence allow for appropriate modifications, consistent with the overall objectives of the study. 

The intervention in this trial was developed through in-depth interviews with the target population to ensure its alignment with their cultural values, preferences, and specific barriers to engaging in PA [53]. Utilising the Behaviour Change Wheel, a series of BCTs were identified to enhance participants’ capability, opportunity, and motivation to engage in PA [9, 54]. These techniques were implemented through a package comprising booklets, three workshops, and a social media support group, all tailored to the cultural context of older Chinese adults.

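### The physical-activity eligibility rule is joined by 'or' in the abstract but by 'and' in the inclusion criterion, and the exclusion thresholds do not match the guideline.

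*Protocol article*

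**What the plan says.** The Protocol article describes the activity requirement in several places.

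- Abstract, Methods/design: people are eligible if they fall short of the WHO recommendations, spelled out as "< 150 min moderate PA or balance/strength exercise < 2 times per week".
- Eligibility criteria, inclusion: the lead-in is "Self-report not meeting the PA guidelines for older adults". The bracket after it defines this as "engaging in less than 150 min of moderate-level PA each week and performing balance, strength, and flexibility exercises less than twice a week".
- Eligibility criteria, exclusion: people who already meet the guidelines are removed, defined as "engaging in more than 150 min of moderate-level PA each week and performing balance, strength, and flexibility exercises more than twice a week".
- Control group (WHO leaflet group): the recommendation itself is given as "150–300 min of moderate or 75–150 min of vigorous aerobic activity per week, along with balance and strength exercises twice weekly".
- Discussion: "The study specifically targets older Chinese adults who do not currently meet recommended PA guidelines".

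No section reconciles the 'or' with the 'and'.

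**The concern.** The guideline has an aerobic part and a balance and strength part, and both are needed to meet it. Failing it therefore means missing at least one part, which is what the abstract says. The inclusion bracket instead asks for both to be missed, which is a narrower population.

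The criterion decides who enters the trial, and it feeds a progression decision. Table 4 sets recruitment at 30 or more within eight weeks for go, 16 to 29 for amend and 15 or fewer for stop. The Discussion also drops eligibility as a progression indicator on the ground that most of this population is inactive, which depends on how inactive is defined. If the rule is unclear, a reader planning the full trial cannot tell which population the observed recruitment describes.

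**Working it through.** This is a check of logic. No sample size, power or significance level enters it, and the plan states no figure to reproduce.

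**Inputs.** The thresholds are 150 minutes of moderate activity a week and balance and strength exercise twice a week (Control group section). The three rules are:

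- abstract inclusion: minutes < 150 OR frequency < 2;
- Methods inclusion: minutes < 150 AND frequency < 2;
- Methods exclusion: minutes > 150 AND frequency > 2.

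**Step 1. Cross three levels of each component, giving 3 × 3 = 9 combinations.** For this step, flexibility is treated as part of the balance and strength component.

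| Minutes | Frequency | Meets guideline | Abstract includes | Methods includes | Methods excludes |
|---|---|---|---|---|---|
| < 150 | < 2 | no | yes | yes | no |
| < 150 | = 2 | no | yes | no | no |
| < 150 | > 2 | no | yes | no | no |
| = 150 | < 2 | no | yes | no | no |
| > 150 | < 2 | no | yes | no | no |
| = 150 | = 2 | yes | no | no | no |
| = 150 | > 2 | yes | no | no | no |
| > 150 | = 2 | yes | no | no | no |
| > 150 | > 2 | yes | no | no | yes |

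**Step 2. Count.**

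- The abstract includes 5 combinations and the Methods criterion includes 1. The difference is 5 − 1 = 4, and in all four the person meets exactly one part of the guideline.
- The guideline is met in 4 combinations. The exclusion names 1 of them. The other 4 − 1 = 3 sit at a threshold and are missed because the exclusion says 'more than' where the guideline needs 'at least'.
- Combinations named by neither Methods criterion: 9 − 1 − 1 = 7, which is the 4 plus the 3.

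These are counts of logical combinations, not of people.

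**Step 3. Compare the wording.** Both Methods brackets include flexibility. The abstract and the recommendation in the Control group section do not.

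**Step 4. Test the repair.** Include if minutes < 150 OR frequency < 2, and exclude if minutes ≥ 150 AND frequency ≥ 2. This gives 5 included, 4 excluded and 9 − 5 − 4 = 0 left over. If the narrower population is meant, include if minutes < 150 AND frequency < 2, and exclude if minutes ≥ 150 OR frequency ≥ 2. This gives 1 included, 8 excluded and 0 left over. Either pair is coherent; the present pair is not.

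**The case against.** **The status of these people is not open.** A reader might infer that the seven combinations named by neither criterion are people whom the Methods cannot classify. That goes too far. Anyone who fails an inclusion criterion is not enrolled, whatever the exclusion list says, so the Methods taken literally do give an answer: they stay out. This objection stands. What remains is that the abstract gives the opposite answer for four of the seven, and that the exclusion does not describe the group it is meant to remove.

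**Most of the text points one way.** The lead-ins to the two criteria, not meeting against already meeting, are complements, and they agree with the abstract and the Discussion. The bracketed 'and' may be a slip in negating a two-part guideline. This is plausible, but the bracket is the operational definition, and a screener following it would turn away people whom the abstract admits.

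**The Table 2 interviewee.** In the Otago Exercise Booklet row, an interviewee says "I only walk, and I walk at least half an hour a day. I don’t know how to do strength and balance exercises". A reader might infer that the 'and' rule shuts out the very person for whom that component was written. Daily walking of 30 minutes is 7 × 30 = 210 minutes a week, but the intensity is not given and the threshold counts moderate activity only. If the walking is lighter than moderate, this person misses both parts and can be included under either rule. The example shows that such a case is possible and no more.

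**Vigorous activity.** The stated recommendation has a vigorous route that the criteria do not mention. A reader might count this as a further contradiction. It is not one, since the abstract and the criteria both use moderate minutes only; it is a simplification that they share.

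**No formal inference depends on the rule.** The Data analysis section plans no hypothesis test or between-group comparison, and both arms come from the same screened pool. This stands: the problem concerns who is recruited and how recruitment is read, not the validity of the randomised comparison.

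**Conclusion.** The concern holds as an inconsistency in the trial's defining eligibility rule. It has three parts:

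- the 'or' of the abstract against the 'and' of the inclusion bracket;
- an exclusion whose 'more than' misses people exactly at a threshold;
- a flexibility element found only in the Methods brackets.

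The first is the substantive one, because it changes who can enter. The other two are drafting faults that should be corrected with it. The article states these rules outright, so this is not detail left to a longer document.

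Its size in people is unknown. The article gives no share of older Chinese adults who meet exactly one part of the guideline, so any percentage loss from the recruitment pool would be a guess. A reader might infer that the recruitment target is at risk. The documents do not show that: the Discussion calls eligibility easy to satisfy, while the Sample size section calls inactive people hard to recruit, and neither gives data.

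The conclusion rests on reading the guideline as two parts that must both be met, as the Control group section states it.

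**What to change.** State one rule and use it in the abstract, the inclusion and exclusion criteria, and the screening form. The version that fits the criterion's own lead-in is to include people with less than 150 minutes of moderate activity a week OR balance and strength exercise less than twice a week, and to exclude those with at least 150 minutes AND at least twice a week. Remove flexibility, or use it in every statement of the rule.

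If the team intends the narrower population that misses both parts, that is its choice. In that case the abstract should say 'and', the exclusion should cover anyone who reaches either threshold, and the lead-in and the Discussion should no longer describe the population simply as not meeting the guidelines.

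The Trial status section says recruitment was in progress at submission. The report should therefore state which rule was applied at screening, and whether it changed, so that the recruitment count can be read against a known population.

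The cost is a short wording amendment and one sentence in the report, with no added burden on participants. If screening used the 'and' rule and the team adopts 'or', later entrants may include people who meet one part, and the report should say when the change took effect.
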